**Fig. 3 Fig3:**
[figure not shown]
Study procedures in the LUTIA trial

#### Treatment

After providing informed consent, patients will be randomized to IA treatment of either the left or the right liver lobe. A complete treatment consists of four cycles of ^177^Lu-DOTATATE every 6 to 12 weeks [18]. On the day of treatment, patients will be hospitalized for one day and one night. Laboratory examination will be performed to ensure no toxicities have occurred and that the patient is fit for treatment and angiography. Prior to or at the start of the angiography procedure, co-infusion of amino acids (1 L 2.5% lysine/arginine during 4 h) is initiated and prophylactic oral anti-emetics (ondansetron 8 mg) are given. During the angiography, the allocated hepatic artery (i.e., left or right) will be catheterized via a femoral or radial approach. A nuclear medicine physician and interventional radiologist will determine the final injection position during angiography. In the first angiographic procedure, a cone-beam computed tomography (CBCT) scan will be performed with a catheter position identical to the injection position. The CBCT confirms the target tumor’s arterial blood supply and demonstrates the arteries’ perfusion territory. Next, 7400 MBq of ^177^Lu-DOTATATE is administered in 30 min, according to the instructions for use of Lutathera [19]. During every cycle, the same injection position is used (i.e., the same randomly allocated liver lobe is IA-treated four times).

All (serious) adverse events will be monitored and logged by medical personnel. A post-treatment ^177^Lu-DOTATATE SPECT/CT scan and total-body planar scintigraphy will be acquired 24 h (± 3 h) post-injection. The acquisition of the SPECT/CT scan after the first cycle is essential for the main study objective, while the SPECT/CT scans after the second, third, and fourth cycles will provide information on the secondary study objectives.

#### Follow-up

A control visit will be scheduled 4 to 7 weeks after each administration. At 3 and 6 months after completion of all four cycles, a control visit is scheduled and a contrast-enhanced diagnostic CT in combination with a ^68^Ga-DOTATOC PET/CT is performed. During all visits, laboratory investigations are performed to assess biochemical and hematological toxicity. Furthermore, patients will undergo physical examination and WHO performance status assessment.

### Objectives

The primary objective is to evaluate whether there is a difference in T/N activity concentration ratio on post-treatment SPECT/CT between the IA- and IV-treated liver lobes. As secondary objectives, activity concentration ratios and absolute mean values of tumor- and healthy liver-absorbed doses in the two lobes will be calculated and compared. Other secondary objectives include the post-treatment tumor response, dose-response relation, and post-treatment hepatic, hematologic, and renal toxicity. Activity concentration in contralateral liver tumors and extrahepatic tumor depositions and renal activity will also be assessed.

### Outcome assessment

To determine the T/N activity ratio on post-treatment SPECT/CT, volumes of interest (VOIs) are drawn based on the pre-treatment contrast-enhanced CT or magnetic resonance imaging (MRI) scan. Only tumors with a minimal diameter of 3 cm are delineated, up to three tumors per liver lobe. For the normal liver tissue VOIs, a representative portion of the normal liver tissue is delineated in each liver lobe, with a minimal diameter of 3 cm. Of all delineated VOIs, the mean number of counts per voxel is calculated.

For the secondary endpoints, a dose-point kernel in commercially available software will be used to calculate the mean absorbed dose, based on the 24-h post-treatment SPECT/CT and mean effective half-life of ^177^Lu-DOTATATE [20, 21]. Comparisons are made between the IA and IV groups by means of a Student *t* test or Mann-Whitney *U* test, where appropriate. Tumor response is assessed on contrast-enhanced CT or MRI using the Southwest Oncology Group (SWOG) solid tumor response criteria, Response Evaluation Criteria In Solid Tumors version 1.1 (RECIST 1.1) and modified Response Evaluation Criteria in Solid Tumors (mRECIST) [22–24]. Response to treatment is assessed on both the patient and liver levels. Moreover, biochemical response will be evaluated using chromogranin A (CgA) levels, measured at baseline and during follow-up. Biochemical, hematological, and clinical toxicity will be graded according to the Common Toxicity Criteria on Adverse Events (CTCAE) version 4.03 [25].

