### Trial design

The Lutetium Intra-Arterial (LUTIA) study is a multicenter, open-label, phase II, within-patient RCT. The study design differs from the standard parallel-group design, in which patients are allocated by randomization to either the treatment or the control group [16]. Instead, patients will act as their own control, by treating only half of the liver by IA administration of ^177^Lu-DOTATATE. Via the systemic circulation, the contralateral lobe and extrahepatic disease will be treated as if by IV administration (second-pass effect; see Fig. 1). ^177^Lu-DOTATATE activity in tumors in the IA-treated lobe will be compared with the activity in tumors in the contralateral lobe (IV-treated).

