### Sample size assessment

The intended sample size is calculated using a paired samples *t* test on the difference in T/N uptake ratio between the IA-treated and contralateral lobes, which is equivalent to a one-sample *t* test on the within-patient difference scores. Assuming a moderate to large effect (i.e., $$\text{d}_{z}={\mu}_{diff}/{\sigma}_{diff}= 0.65  $$), a one-sided α of 0.025, and using a sequential testing procedure with an O’Brien-Fleming type error spending function, a power of approximately 0.9 is obtained with futility boundary values equal to T_1_ = − 0.1045056 and T_2_ = 2.045732 for an interim analysis at n_1_ = 10 and final analysis at n_2_ = 26. Interim analysis will therefore be performed after ten patients have been treated, and final analysis will be performed after 26 patients have been treated.

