### Statistical analysis

Continuous variables, such as the primary outcome (i.e., T/N ratio), will be described by means and standard deviations. The mean T/N ratios will be compared between the IA- and IV-treated lobes by means of a paired *t* test. Categorical variables, such as the response after treatment, will be compared by means of a chi-square or Fisher’s exact test, depending on group size.

All statistical tests will be performed two-sided. A *p* value of < 0.05 will be considered statistically significant.

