To date, no prospective study on IA administration has been performed. A small number of studies, using different radiopharmaceuticals, have shown a beneficial effect [15]. The first study, performed by McStay et al*.*, showed no additional toxicity when administering yttrium-90 (^90^Y)-DOTA-lanreotide IA [26]. In three publications by Limouris and colleagues, promising results were reported with response rates of ~ 50% [27–29]. Kratochwil et al. found a partial response in 8/15 patients and a complete response in 1/15 patients after IA treatment with a combination of ^90^Y- and ^177^Lu-DOTATOC [30]. The same authors previously reported significantly enhanced tumor uptake of the diagnostic radiotracer ^68^Ga-DOTATOC after IA administration [31]. In a non-randomized crossover-like study, they performed a ^68^Ga-DOTATOC PET/CT after IV administration and, subsequently, a ^68^Ga-DOTATOC PET/CT after IA administration. Standardized uptake values in NETs were approximately 3.75 times higher after IA administration. Comparable enhancement of activity concentration in liver metastases was also shown by Pool et al., in a similar crossover-like study in three patients treated with indium-111-DTPA-octreotide, both IV and IA [32]. Up to a 2.4-fold higher concentration in tumors was quantified. In the available literature, no additional side effects were observed.

To our knowledge, the LUTIA study is the first RCT to investigate the effect of IA administration of ^177^Lu-DOTATATE in patients with NETs. Previously performed studies lacked comparison with IV administration. In the LUTIA study, a direct comparison can be made between IV and IA administration within the same patient. Consequently, between-patient differences have little to no effect on the difference in T/N activity ratios. This is a great advantage of this study design with within-patient randomization, since NETs are known to be very heterogeneous. The heterogeneity of tumor characteristics (such as tumor subtype, growth rate, SSTR-2 expression, functional state, and imaging characteristics) causes difficulty when performing comparative research on NETs [33]. Within-patient comparison automatically corrects for any differences in tumor characteristics between patients. Furthermore, the paired design increases power in statistical analysis, and fewer patients need to be treated to notice an effect.

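### The secondary comparison of absorbed dose between the IA and IV lobes is planned with tests for independent groups, although both lobes belong to the same patient

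*Protocol article*

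**What the plan says.** The trial is randomized within patients. Under Trial design, "patients will act as their own control, by treating only half of the liver by IA administration", and the other lobe serves as the intravenous comparator. The Objectives section carries this over to the secondary endpoint: "absolute mean values of tumor- and healthy liver-absorbed doses in the two lobes will be calculated and compared".

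Outcome assessment explains how mean absorbed dose is derived from the 24-hour SPECT/CT, and then gives the test: "Comparisons are made between the IA and IV groups by means of a Student" t test, with the Mann-Whitney U test as the alternative.

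For the primary endpoint the article does name a paired method. Statistical analysis states: "The mean T/N ratios will be compared between the IA- and IV-treated lobes by means of a paired *t* test". The sample size section uses the same paired test. The Discussion gives the reason for the design: "the paired design increases power in statistical analysis, and fewer patients need to be treated to notice an effect".

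No section assigns a paired test to absorbed dose.

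**The concern.** Mann-Whitney U is a test for two independent samples; its paired counterpart is the Wilcoxon signed-rank test. A Student t test between groups is, on its natural reading, also the independent-samples form. Applied here, both would treat the 52 lobes (26 × 2) of 26 patients as unrelated. The differences between patients, which the design is meant to remove, would go back into the error term.

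Absorbed dose is the secondary endpoint closest to the trial's stated aim of raising the tumor-absorbed dose in liver metastases. With positive correlation between the lobes of a patient, a real dose gain could be reported as non-significant beside a positive T/N result, only because of the test chosen.

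**Working it through.** **Inputs from the article.** 26 patients; standardized within-patient difference dz = 0.65, assumed for the T/N ratio; one-sided α of 0.025 for the sample size; two-sided 0.05 for the tests; stated power about 0.9 (Sample size assessment, Statistical analysis).

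**Inputs assumed.** The correlation ρ between the two lobes of a patient is not in the article, so it is varied from 0 to 0.8. No effect size is given for absorbed dose, so dz = 0.65 is borrowed from the T/N ratio. Lobe values are taken as bivariate normal with equal variances.

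**Step 1: the plan's own figure.** For the paired t test the noncentrality is 0.65 × √26 = 3.314, and the critical value on 25 degrees of freedom is 2.060. Power is 0.890. Simulating the two-stage procedure with the stated boundaries (−0.1045 at 10 patients, 2.0457 at 26) gives power 0.888 and one-sided type I error 0.025. The stated power of about 0.9 is reproduced, and it rests on pairing.

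**Step 2: what the unpaired test does.** With common lobe standard deviation σ, the variance of the mean difference is 2σ²(1 − ρ)/n. The paired test estimates this. The unpaired test estimates 2σ²/n, so its standard error is too large by a factor 1/√(1 − ρ). Its critical value, on 50 degrees of freedom, is 2.009. The ratio of unpaired to paired interval width is therefore

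(2.009/2.060) × 1/√(1 − ρ) = 0.975/√(1 − ρ).

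At ρ = 0.5 this is 0.975/0.707 = 1.38.

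**Step 3: power and type I error.** These come from simulation of 26 pairs (200,000 trials per setting, two-sided 0.05). Holding dz at 0.65 sets the raw difference, in units of σ, to 0.65 × √(2(1 − ρ)).

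| Assumed ρ | Raw difference / σ | Power, paired t | Power, unpaired t | Type I error, unpaired t | Interval width ratio |
|---|---|---|---|---|---|
| 0 | 0.92 | 0.89 | 0.90 | 0.05 | 0.98 |
| 0.3 | 0.77 | 0.89 | 0.82 | 0.02 | 1.17 |
| 0.5 | 0.65 | 0.89 | 0.68 | 0.007 | 1.38 |
| 0.7 | 0.50 | 0.89 | 0.38 | 0.001 | 1.78 |
| 0.8 | 0.41 | 0.89 | 0.16 | 0.0001 | 2.18 |

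Mann-Whitney U behaves alike: power 0.89, 0.79, 0.65, 0.36 and 0.16 in the same order, against about 0.88 for the Wilcoxon signed-rank test.

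**Step 4: sensitivity to the effect size.** At dz = 1.0 the unpaired t test still has power 0.98, 0.91 and 0.71 at ρ = 0.5, 0.7 and 0.8. At dz = 1.3 it has 1.00, 1.00 and 0.97.

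**The case against.** **The wording could mean a paired t test.** Taken alone, the term Student t test allows that. The stated alternative does not, and where the authors mean a paired test elsewhere they say so. This defence is weak.

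**The details can be left to the analysis plan.** An omission could be. Here the article names tests, and at least one of the two does not fit the design. An analysis plan that followed the sentence would carry the error forward.

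**The size is uncertain.** This stands. Neither ρ nor an effect size for absorbed dose is documented. At ρ = 0.3 the loss is modest and at ρ = 0 there is none. The Discussion cites uptake roughly 2.4 to 3.75 times higher after IA administration in earlier work, so an effect well above dz = 0.65 cannot be excluded. A reader might infer from the lower rows of the table that the test is bound to be severely conservative; the article does not support that without conditions.

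**The scope is narrow.** This also stands. A reader might infer that every secondary lobe comparison is unpaired. The sentence follows directly on the absorbed-dose calculation, and the paired t test under Statistical analysis is written for mean T/N ratios in general, so it can cover secondary T/N comparisons.

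**Tumors as the unit.** Up to three tumors per lobe are delineated, and a reader might infer that they would be tested as independent observations. The article does not state the unit for this comparison, so that is not a finding. Nor does the sentence promise confidence intervals; their width is a consequence of the method.

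**Conclusion.** The sentence is wrong as written for absorbed dose: it prescribes tests for independent groups for data that are paired by design. With positive within-patient correlation, which the Discussion's rationale for the design presumes, the error is conservative. Over the assumed range of ρ from 0 to 0.8 at dz = 0.65, power goes from no loss to a fall from 0.89 to 0.16, and the interval width ratio runs from 0.98 to 2.18. These figures depend on the assumed ρ and the borrowed dz, and the loss shrinks as the effect grows.

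A reader might infer that false-positive dose findings are likely. At lobe level with zero or positive correlation they are not: type I error stays at or below 0.05. Only a negative correlation would raise it (to about 0.085 at ρ = −0.3), and the design rationale points the other way.

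A reader might also infer that the trial's main result is at risk. It is not: the primary comparison and the sample size are both paired. The point concerns one secondary endpoint of a phase II trial and should be fixed, but it does not threaten the trial's main conclusion.

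**What to change.** Replace the test sentence under Outcome assessment with:

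> Absorbed doses in the IA- and IV-treated lobes are compared within patient by a paired t test or, where appropriate, a Wilcoxon signed-rank test, on one value per lobe.

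If tumors or treatment cycles are to be analysed as separate units, use a mixed model with a random effect for patient, and for lobe within patient.

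The cost is one sentence in the protocol or analysis plan, settled before the secondary endpoints are analysed. No new data, visits or patients are needed, since both lobes are already measured in every patient.

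### At the patient and liver levels named for tumor response no IA-versus-IV comparison exists, and at lobe level chi-square or Fisher's test would ignore the pairing

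*Protocol article*

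**What the plan says.** Under Trial design, "patients will act as their own control, by treating only half of the liver by IA administration", and "the contralateral lobe and extrahepatic disease will be treated as if by IV administration". Under Treatment, "patients will be randomized to IA treatment of either the left or the right liver lobe", and in every cycle "the same randomly allocated liver lobe is IA-treated four times". The randomized contrast is thus between two lobes of one liver, with no switch of side.

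On response, the Objectives section reads: "Other secondary objectives include the post-treatment tumor response, dose-response relation, and post-treatment hepatic, hematologic, and renal toxicity". Outcome assessment adds: "Tumor response is assessed on contrast-enhanced CT or MRI using the Southwest Oncology Group (SWOG) solid tumor response criteria", together with RECIST 1.1 and mRECIST, and then: "Response to treatment is assessed on both the patient and liver levels". Statistical analysis says: "Categorical variables, such as the response after treatment, will be compared by means of a chi-square or Fisher’s exact test, depending on group size". The sentence just before that one gives the T/N ratio a paired t test between the lobes.

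**The concern.** A chi-square or Fisher's exact test needs two separate groups of units. At patient or liver level each unit contains both the IA lobe and the IV lobe. The only groups that randomization creates at those levels are IA-left and IA-right, and that contrast is not the trial's question.

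At stake is the step from uptake to benefit. The Discussion argues that higher activity in liver metastases may lead to better response, and that positive results will lead to a large RCT. The randomized evidence this trial can offer on that step is the comparison of response between the two lobes. The stated levels do not deliver it, and the stated tests do not suit it.

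**Working it through.** **1. The plan's own figure.** The article gives no rate, power or correlation for response. Its only power figure is for the primary endpoint (paired t test, d_z = 0.65, one-sided 0.025, analyses at 10 and 26 patients, power about 0.9). It reproduces: fixed-design power at n = 26 is 0.890. The two-stage rule with the stated boundaries gives power 0.887 and one-sided error 0.0250. The point below does not touch it.

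**2. Response at the stated levels.** Count units by route received:

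| Level | IA and IV | IA only | IV only |
|---|---|---|---|
| Patient | 26 | 0 | 0 |
| Liver | 26 | 0 | 0 |

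Both groups of the wanted 2×2 table are empty, so no statistic for IA against IV can be computed. This is logic and needs no assumption.

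**3. Response read as lobe level.** There are now 26 pairs. Assume response of 50% in IA lobes and 20% in IV lobes. Let each lobe respond when a normal liability falls below its threshold, with latent correlation ρ between the two lobes. Then:

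- p11 = Φ₂(Φ⁻¹(0.5), Φ⁻¹(0.2); ρ) is the chance that both respond.
- p10 = 0.5 − p11 (IA lobe only) and p01 = 0.2 − p11 (IV lobe only).
- True variance of the difference in proportions = [0.25 + 0.16 − 2(p11 − 0.10)]/26.

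At ρ = 0, p11 = 0.100, the variance is 0.41/26 = 0.0158 and the standard error is 0.126. At ρ = 0.7, p11 = 0.179, the variance is (0.41 − 0.158)/26 = 0.0097 and the standard error is 0.098. An unpaired test keeps using 2 × 0.35 × 0.65/26 = 0.0175 (standard error 0.132) whatever ρ is. That is why it does not gain from the pairing.

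Summing the multinomial probabilities of all possible tables of 26 pairs, at two-sided 0.05 (simulation agrees within 0.01):

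| Power, 50% vs 20% | ρ = 0 | 0.3 | 0.5 | 0.7 | 0.85 |
|---|---|---|---|---|---|
| Fisher | 0.54 | 0.54 | 0.54 | 0.54 | 0.53 |
| Chi-square, uncorrected | 0.65 | 0.67 | 0.68 | 0.69 | 0.70 |
| Exact McNemar | 0.50 | 0.58 | 0.65 | 0.74 | 0.81 |
| Mid-p McNemar | 0.60 | 0.68 | 0.75 | 0.83 | 0.90 |

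**4. Error rate with no true difference** (30% assumed in both lobes, same model):

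| Size at nominal 0.05 | ρ = 0 | 0.3 | 0.5 | 0.7 |
|---|---|---|---|---|
| Fisher | 0.025 | 0.013 | 0.007 | 0.002 |
| Chi-square, uncorrected | 0.055 | 0.035 | 0.021 | 0.009 |
| Exact McNemar | 0.023 | 0.021 | 0.018 | 0.012 |
| Mid-p McNemar | 0.042 | 0.040 | 0.037 | 0.030 |

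For correlated lobes the unpaired tests err on the conservative side. They do not manufacture false positives.

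**The case against.** Several objections have force.

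- **The level.** A reader might infer that response is scored only for the whole liver. The article does not say so: it names two levels and excludes no other, and the full protocol may define a lobe level. The natural reading still favors the concern, because the article says lobe wherever it means lobe, including in the same section.
- **The contrast.** The Objectives section ties the lobe comparison to activity and absorbed dose and lists response without it. A response rate for a cohort that all received the same regimen is a valid description. But Statistical analysis says response will be compared, without naming groups, and IA versus IV is the comparison the trial exists to make.
- **Legitimate uses of the tests.** Chi-square or Fisher would be proper for between-patient groups, for example response by dose category under the dose-response objective. That stands, but does not supply an IA-versus-IV comparison.
- **Lost information.** A reader might conclude that the trial can never say whether the IA lobe responded better. That goes too far. Contrast-enhanced CT is scheduled at 3 and 6 months after the last cycle, and each patient must have a lesion of at least 3 cm in each lobe, so the contrast is recoverable.
- **The size of the gain.** At zero correlation exact McNemar has no advantage over Fisher (0.50 against 0.54). Against uncorrected chi-square it leads only at the higher correlations shown (0.74 against 0.69 at ρ = 0.7), and mid-p McNemar is level at 0.3 and ahead from 0.5. The case for a paired test at low correlation is validity, not power.

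The two halves of the concern are also alternatives: either no table exists, or one exists and the test is wrong. Both cannot describe the same plan, but each reading needs a correction if IA is to be compared with IV.

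**Conclusion.** The point holds in limited form. At patient and liver level the IA-versus-IV comparison of response cannot be formed, whatever the data. At lobe level the named tests ignore the pairing that the design is built on. They are then conservative, and less powerful than mid-p McNemar when within-patient correlation is moderate or high: at ρ = 0.7, 0.83 against 0.54 for Fisher and 0.69 for chi-square. These power figures rest on assumed rates of 50% and 20% and an assumed correlation.

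A reader might take this for a flaw that must be cured before the trial can be trusted. The article does not support that. It concerns one secondary endpoint with no stated power, the direction of error is conservative, and the primary T/N endpoint is defined by lobe and tested with a paired t test. It is worth correcting, but ranks below an essential change.

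**What to change.** - **Outcome assessment:** add a lobe-level response, scored on target lesions within the IA lobe and, separately, within the contralateral lobe, from the CT or MRI already planned.
- **Statistical analysis:** for the IA-versus-IV comparison of response, replace chi-square or Fisher with McNemar's test, naming the mid-p or the exact form in advance. Analyze percentage change in lobe tumor size with a paired t or signed-rank test. Keep chi-square or Fisher only for comparisons between separate groups of patients, and name those groups.
- **Patient- and liver-level response:** report descriptively.

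The cost is a few sums by lobe from lesions already measured and a change of wording. No further imaging or patients are needed. The change should be made before response data are examined.
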